### **SAMPLE SIZE JUSTIFICATION:**

The original study was designed to test for a 20% absolute improvement in the rate of grade  $\geq 2$  radiation morbidity (subcutaneous tissue fibrosis, joint stiffness, or edema at 2 years ( $\pm 3$  months) from 37% in the preoperative RT arm of the CAN-NCIC-SR2 study to 17% which requires 41 patients per cohort with 5% type I error and 80% statistical power. Allowing for 20% of patients being ineligible or not analyzable at 2 years, the total sample size needed is 51 patients. **The study met this initial endpoint(6).**

**The expansion cohort** of this study aims to evaluate non-inferiority of major wound complication rate in cohort B (neoadjuvant chemotherapy and radiotherapy) versus patients in cohort A (radiotherapy alone). One-sided two-sample proportion test will be carried out to assess the non-inferiority of major wound complication rate in cohort B compared to cohort A. According to a recent study on rates of wound complications in patients receiving preoperative RT(8), we assume the wound complication rate in cohort A to be 21% (79% success rate). We also assume that for every patient enrolled in cohort B, at least three patients will be enrolled in cohort A. With significance level 0.1 and power 80%, the enrollment of at least 41 patients in cohort B will enable us to detect a 15% increase in the wound complication rate of cohort B, which would translate to a 36%

wound complication rate (64% success rate)(9). A wound complication rate of 36% has previously been considered acceptable for patients receiving standard preoperative radiotherapy and surgery(2). We set the minimum enrollment number to 123 for cohort A and 41 for cohort B. To account for a 20% rate of potential screening failures or participant dropouts, the total enrollment goal for the expansion cohort is 205 patients.

### **FUNDING, REGULATORY, AND FEASIBILITY ISSUES:**

UCLA Dept. of Radiation Oncology has the capability, equipment, and expertise to perform this external beam radiation therapy treatment.

### **PATIENT ACCEPTABILITY/ETHICS AND CONSENT ISSUES:**

Only patients able to give informed consent will be eligible for the trial.

### **SCHEMA**

Diagnosis of soft tissue sarcoma of the extremity/trunk

[figure not shown]

Plan for preoperative radiation treatment

[figure not shown]

5 fractions of radiation (5.0 or 6.0 Gy x 5) delivered daily

[figure not shown]

Surgery within 12 weeks post-radiation

[figure not shown]

Follow-up

#### **Eligibility (EXPANSION COHORT):**

Pathologically confirmed STS of extremity/trunk

Planned preoperative radiotherapy

#### **Primary Endpoint:**

Non-inferiority of major wound complication rate  
(cohort B vs cohort A)

#### **Cohort A**

No neoadjuvant chemotherapy

#### **Cohort B**

Neoadjuvant chemotherapy

[figure not shown]

## **1.0 OBJECTIVES**

### **1.1 Primary objectives**

#### **1.1.1 Primary endpoint:**

Rate of major wound complications per the criteria set forth in Appendix

### **1.2 Secondary objectives**

#### **1.2.1 Secondary endpoints:**

Grade  $\geq 2$  radiation morbidity (subcutaneous tissue fibrosis, joint stiffness, or edema) at 2 years

Evaluate local control, regional control, distant metastasis, progression free survival, and overall survival

Evaluate the functional outcomes as assessed using the musculoskeletal tumor rating scale (MSTS) and the Toronto Extremity Salvage Score (TESS)

### **1.3 Exploratory objectives**

Collect germ-line DNA and nucleic acids from cancer patients to further investigate the association and identify new germ-line mutations that impact cancer predisposition

Investigate the role of germ-line mutations in predicting cancer outcome, toxicity, and response to therapy

Evaluate pre-treatment, post-radiotherapy and, if applicable, metastatic or relapse tissue specimens for characteristics including DNA alterations, gene expression, protein expression, immunophenotype and Intratumoral heterogeneity that may be predictive, prognostic or explain resistance.

## **2.0 BACKGROUND**

Randomized data demonstrates that radiation therapy improves local control after surgical resection in extremity/trunk soft tissue sarcomas(1). Some advantages have been observed however with the administration of pre-operative compared with post-operative radiation. This includes a reduction in late term lymphedema, fibrosis and joint stiffness but comes at the cost of increased acute wound complications. Given that wound complications are temporary whereas lymphedema, fibrosis, and joint stiffness are permanent injuries many groups prefer to deliver pre-operative radiation.

The standard dose for pre-operative radiation therapy is 45-50 Gy delivered daily over the course of about 25 treatments. This is an effective treatment however it is inconvenient for patients to come daily for treatment over 5 weeks. This means that many patients receive their radiation therapy in the community under the care of a physician who may see only a few sarcomas each year whereas a radiation oncologist at a specialized sarcoma center may see as many as 5 new sarcoma patients in a week. Furthermore, it would be advantageous if patients were to receive all of their care (i.e. radiation and surgery) in one specialized sarcoma center, where the treating physicians are in close contact allowing for less disjointed care.

Recent advances in radiation treatment now allow for higher doses per treatment to be delivered safely. Reductions in the total duration of radiation treatment are now standard of care for breast and prostate cancer. Advances in the reduction of treatment duration for sarcomas are lacking.

We have now completed our initial analysis of the first 52 patients treated on this 5-day protocol, with encouraging results in terms of local control and toxicity(6). We chose a dose (30 Gy delivered over 5 fractions) that would be biologically equivalent to the conventional radiotherapy dose of 50 Gy delivered over 25 fractions. This was calculated based on the linear quadratic formula, where biological effect (E) is determined by the number of fractions (N) and size of the dose per fraction (d) using the formula  $E = (d + \alpha\beta d^2)Nd$ . The  $\alpha/\beta$  ratio for STS is presumed to be 4. The 5 fraction dose roughly equivalent to 50 Gy administered in 25 fractions is approximately 30 Gy (6 Gy x 5). The 5 fraction dose roughly equivalent to 28 Gy administered in 8 fractions (which is a regimen often used for patients receiving chemotherapy) is approximately 25 Gy (5 Gy x 5).

### **3.0 PATIENT SELECTION**

#### **3.1 Conditions for patient eligibility**

- 3.1.1 Histologically confirmed soft tissue sarcoma of the extremity/trunk
- 3.1.2 Planning to undergo standard preoperative radiotherapy
- 3.1.3 Resectable primary lesion (patients with pre-existing metastasis will be included if their primary is still going to be resected)
- 3.1.4 Age  $\geq 12$
- 3.1.5 KPS  $\geq 70$  or ECOG of 0 - 2
- 3.1.6 If a woman is of childbearing potential, a negative serum or urine pregnancy test must be documented.

#### **3.2 Conditions for patient ineligibility**

- 3.2.1 Active treatment of a separate malignancy

### 3.2.2 History of prior irradiation to the area to be treated

## 4.0 REGISTRATION PROCEDURES

### 4.1 General guidelines

Patients seen at UCLA as new patients diagnosed with soft tissue sarcoma who are considering pre-operative radiation treatment will be informed of this clinical trial. The decision to participate will be voluntary. Eligibility will be determined at the time of consultation. The decision not to participate in the trial will not affect the delivery of standard treatment options.

### 4.2 Registration Process

An informed consent form will be given to the patient for review. Consent will be obtained after a clear and thorough discussion between the patient and the study investigator in the clinic. To register a patient, the research coordinator will obtain or complete:

- signed informed consent form;
- signed HIPAA authorization form;
- pathological confirmation of soft tissue sarcoma (UCLA pathology review not required);
- medical history;
- documentation of clinical examination;
- negative serum or urine pregnancy test for women of childbearing potential.

The patient will be enrolled on the study if all eligibility criteria are satisfied; otherwise, the patient will not be enrolled on the study.

## 5.0 TREATMENT PLAN

### 5.1 Radiation Simulation and Planning

Each patient will undergo radiation simulation and planning. A custom vacloc bag, alpha cradle, or equivalent immobilization device will be used. A CT and/or MRI simulation will be obtained with or without IV contrast, which is standard of care for any patient undergoing radiation therapy for soft tissue sarcomas.

The study investigator will be responsible for delineating the gross tumor volume (GTV) using the CT as well as MRI imaging (if available) performed as part of staging. Guidelines for contouring will be as per the currently open NRG trial for sarcomas. In general this suggests a margin of 3 cm in the superior and inferior directions on the gross tumor volume and a 1.5 cm radial expansion. This expansion should also include any suspicious edema as seen on T2 weighted MRI. This clinical target volume (CTV) will be cropped out of natural anatomic boundaries of spread, such as bone and uninvolved muscle compartments. The CTV will then be expanded to a planning treatment volume (PTV) using a 3-5 mm expansion.

A prescription dose of 6 Gy x 5 fractions (30 Gy) will be delivered to at least 95% of the PTV. No more than 10% of the PTV should receive greater than 120% of prescription dose, and areas receiving >110% of the prescription dose should be restricted to the GTV. Intensity modulated radiation therapy (IMRT) planning techniques may be used in order to minimize radiation dose to nearby organs at risk (OAR) but is not required.

Delineation of normal structures including the bone and skin will be performed and verified by the responsible study investigator. The radiation physicist or dosimetrist will optimize the treatment plan prior to approval for treatment. Dose volume histograms (DVH) and normal tissue constraint parameters specified below will be used to judge the plan quality and optimize PTV coverage with OAR sparing prior to approval.

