## **PROTOCOL SYNOPSIS:**

Radiation therapy in either the pre- or post-operative setting is a standard-of-care treatment option for patients with soft tissue sarcomas based on randomized level 1 evidence(1). Pre-operative radiation treatment is favored at many institutions over post-operative treatment, most notably because it allows the delivery of a lower dose of radiation to a smaller volume(2). The standard pre-operative radiation dose is 45-50 Gy delivered in 25 treatment sessions over 5 weeks.

The 5-week course of radiotherapy can be challenging for sarcoma patients, many of whom travel great distances to have their care at specialized tertiary sarcoma centers. Logistical hurdles prevent patients from relocating to these tertiary centers for the duration of their radiation treatment. We proposed a shorter, condensed form of hypofractionated preoperative radiation therapy administered over 5 days.

More condensed forms of radiation therapy have been adopted in the treatment of several malignancies as radiation oncologists can more easily spare normal tissues with modern radiation techniques and image guidance(3, 4). There is also a biological rationale for this approach in sarcoma, a tumor that is less sensitive to smaller RT fraction sizes (lower  $\alpha/\beta$  ratio; (5)). The purpose of this study is to investigate the toxicity and disease control outcomes of a 5-day radiation regimen that is biologically equivalent to the standard 45-50 Gy regimen given over 5 weeks (25 treatments).

We recently completed an initial cohort of this study (n=52), which was limited to patients receiving neoadjuvant radiation therapy alone. Initial findings of this study have been reported after over 2.5 years of follow-up, and indicate acceptable rates of short- and medium-term complications, with promising rates of local control, both on par with rates observed using conventional 5-week preoperative radiation(6).

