**SECONDARY OBJECTIVE (s):**

- Evaluate the 2 year rate of grade  $\geq 2$  radiation morbidity (subcutaneous fibrosis, joint stiffness, or edema) with a 5 fraction radiation regimen that is biologically equivalent to a standard 45-50 Gy regimen given in 25 fractions.
- Evaluate local control, regional control, distant metastasis, progression free survival, and overall survival.
- Evaluate the functional outcomes as assessed using the musculoskeletal tumor rating scale (MSTS) and the Toronto Extremity Salvage Score (TESS),

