#### **INTERVENTION AND MODE OF DELIVERY:**

Hypofractionated radiation will be delivered in the pre-operative setting to patients with soft tissue sarcoma with external beam radiation therapy. Patients in cohort A will receive 6.0 Gy x 5 fractions delivered daily in 5 fractions. Patients in cohort B will receive 5.0 Gy x 5 fractions delivered daily in 5 fractions. Patients will not be treated on weekends or holidays as is standard practice for radiation treatments.

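### Section 5.1 prescribes 30 Gy in 5 fractions without naming a cohort, while the synopsis assigns cohort B 25 Gy in 5

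*Protocol*

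**What the plan says.** **Treatment plan.** Section 5.1 begins with "Each patient will undergo radiation simulation and planning" and later gives one prescription: "A prescription dose of 6 Gy x 5 fractions (30 Gy) will be delivered to at least 95% of the PTV". There is no cohort qualifier. Sections 5.2 to 5.4 (dose constraints, delivery, follow-up) mention neither cohort B nor a 25 Gy prescription.

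**Synopsis.** The intervention paragraph gives cohort A 6.0 Gy x 5 and then says "Patients in cohort B will receive 5.0 Gy x 5 fractions delivered daily in 5 fractions". The stratification paragraph defines cohort B as patients who have neoadjuvant chemotherapy as well as radiotherapy.

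**Schema.** It lists both doses without assigning them: "5 fractions of radiation (5.0 or 6.0 Gy x 5) delivered daily".

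**Background.** Section 2.0 matches 30 Gy in 5 to 50 Gy in 25. Separately, it gives the five-fraction match to 28 Gy in 8, "which is a regimen often used for patients receiving chemotherapy) is approximately 25 Gy (5 Gy x 5".

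**Equivalence statements.** The opening of the synopsis describes a "5-day radiation regimen that is biologically equivalent to the standard 45-50 Gy regimen given over 5 weeks (25 treatments". The first secondary objective evaluates late morbidity "with a 5 fraction radiation regimen that is biologically equivalent to a standard 45-50 Gy regimen given in 25 fractions".

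**The concern.** Section 5.1 and the synopsis give different doses for the same patients, and the protocol has no rule saying which prevails. Section 5.1 is where the coverage and hot-spot rules stand and is the natural source for whoever builds the plan. The synopsis is a summary.

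The primary question is whether major wound complications in cohort B are non-inferior to those in cohort A. Radiation dose is part of the cohort B regimen under test. If Section 5.1 were followed for cohort B, the trial would evaluate 30 Gy after chemotherapy instead of 25 Gy. If planners differed, it would evaluate a mixture. The yearly interim reports are also to give the rate of compliance with protocol treatment, and for cohort B that rate is undefined while two doses stand.

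**Working it through.** **Inputs**
- Cohort B dose in the synopsis: 5 x 5.0 = 25 Gy.
- Dose in Section 5.1: 5 x 6 = 30 Gy.
- Alpha/beta for soft tissue sarcoma: 4 (Section 2.0).
- Reference regimens: 50 Gy in 25 and 28 Gy in 8 (Section 2.0); 45 Gy in 25 as the lower end of the standard range (synopsis).
- Minimum cohort B size: 41 (synopsis).

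**Formula.** With total dose D, dose per fraction d and alpha/beta 4, the equivalent dose in 2 Gy fractions is EQD2 = D x (d + 4) / (2 + 4).

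| Regimen | d (Gy) | Calculation | EQD2 (Gy) |
|---|---|---|---|
| 50 Gy in 25 | 2.0 | 50 x 6 / 6 | 50.0 |
| 30 Gy in 5 | 6.0 | 30 x 10 / 6 | 50.0 |
| 45 Gy in 25 | 1.8 | 45 x 5.8 / 6 | 43.5 |
| 28 Gy in 8 | 3.5 | 28 x 7.5 / 6 | 35.0 |
| 25 Gy in 5 | 5.0 | 25 x 9 / 6 | 37.5 |

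**The protocol's own derivations reproduce.** 30 Gy in 5 equals 50 Gy in 25 exactly. 25 Gy in 5 is about 7% above 28 Gy in 8 (37.5 / 35.0 = 1.07). The exact five-fraction match to 28 Gy in 8 is 4.78 Gy x 5 = 23.9 Gy, so 25 Gy is a fair rounding. By contrast, 30 Gy in 5 is 43% above 28 Gy in 8 (50.0 / 35.0 = 1.43). The derivation for the chemotherapy setting therefore fits the synopsis dose for cohort B and does not fit the Section 5.1 dose.

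**Size of the discrepancy for cohort B**
- Physical dose: 30 / 25 = 1.20, or 20% more.
- EQD2 at alpha/beta 4: 50.0 / 37.5 = 1.33, or 33% more.
- Other alpha/beta values (assumed, to show the range): at 3, 54.0 / 40.0 = 1.35; at 10, 40.0 / 31.25 = 1.28.

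**Could the rest of Section 5 catch the error?** Not dependably. Several limits in Section 5.2 fit a 30 Gy plan. The long-bone maximum of 31.5 Gy, for example, is 105% of 30 Gy but 126% of 25 Gy. Section 5.2 also says that missing a constraint is not a study deviation.

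**Secondary point: the equivalence wording.** At alpha/beta 4 the stated 45-50 Gy range in 25 fractions spans 43.5 to 50.0 Gy EQD2. The 30 Gy regimen lies at its upper end. The 25 Gy regimen, at 37.5 Gy, falls below its lower end (37.5 / 43.5 = 0.86).

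**The case against.** The contradiction itself cannot be argued away: both statements are current, and a prescription dose is not something left to a statistical analysis plan. The objections concern likelihood and weight.

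1. **Staff will probably use the right dose.** The synopsis is explicit and cohort-specific, the schema shows two doses, and Section 2.0 derives both. Section 5.1 reads like text from the original single-dose cohort that was not updated. This lowers the probability of error but not its consequence, because Section 5.1 is the planning section.
2. **It is not certain which text is wrong.** The synopsis says the expansion tests the group's existing 5-day regimen in both groups, and the secondary objective speaks of one regimen equivalent to 45-50 Gy. Both fit a single 30 Gy dose. The synopsis paragraph is more specific and Section 2.0 supports it, so 25 Gy remains much the likelier intention. The investigator should still confirm it.
3. **The opening of Section 5.1 governs simulation and planning, not the prescription.** This is correct. The contradiction rests on the missing cohort qualifier.
4. **The hot-spot rule adds nothing independent.** Section 5.1 says "areas receiving >110% of the prescription dose should be restricted to the GTV". A 30 Gy plan scored against 25 Gy would put at least 95% of the PTV at or above 120% of prescription and break that rule. But a planner following Section 5.1 prescribes 30 Gy and breaks nothing. The point only restates 30 / 25 = 1.20.
5. **The 33% is not a measure of wound risk.** Alpha/beta 4 is given for the tumour, and the protocol gives none for wound healing. This stands. The 20% physical-dose difference needs no such assumption.
6. **The synopsis purpose statement may describe only the original cohort.** That is a fair reading, since it comes before the expansion is introduced. The secondary objective is not so limited.

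**Conclusion.** The concern holds and must be fixed. As written, Section 5.1 contradicts the synopsis on cohort B's prescription by 5 Gy, which is 20% of the specified dose and 33% in EQD2 at the protocol's alpha/beta of 4. It could affect every cohort B patient, at least 41, and it bears on the regimen compared in the primary endpoint. That 25 Gy is the intended dose is an inference from the synopsis and Section 2.0; it is strong but needs confirmation. Nothing in the document shows that any patient received the wrong dose, and no conclusion about the size of any change in wound-complication rate is drawn. This is an internal inconsistency, not a criticism of the design. The equivalence wording is a minor, separate correction on which the main finding does not depend.

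**What to change.** 1. Amend the prescription sentence in Section 5.1 to read 6 Gy x 5 (30 Gy) for cohort A and 5 Gy x 5 (25 Gy) for cohort B, after the investigator confirms the cohort B dose. The 110% and 120% limits are relative to prescription and will then scale by themselves.
2. Check the prescribed and delivered dose for any cohort B patients already treated.
3. In the same amendment, review whether the absolute limits in Section 5.2 suit a 25 Gy plan.
4. In the first secondary objective, restrict the claim of equivalence to 45-50 Gy in 25 fractions to the 30 Gy regimen. In the synopsis purpose statement, make the same restriction or say that it refers to the original cohort.

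The cost is a one-sentence clarifying amendment, two small wording changes, a review of the dose limits and a check of treatment records. Design, sample size and analysis stay as they are.

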## **5.2 Organs at Risk (OAR) Dose Constraints/Normal Tissue Constraints**

Dose constraints will be used during radiation planning to minimize risk of toxicity. Dose constraint guidelines are shown below, and the treating physician will weigh meeting these constraints with any loss in coverage of the PTV. These constraints are designed as guidelines and failing to meet any of these constraints will not be considered a study deviation. Priority of constraints will depend on the precise anatomic location of the tumor.

### **Organs at risk:**

- Total Skin within field (the superficial 5mm of tissue starting at the air/skin interface and encompassing the PTV): V12 Gy < 50%, V10Gy ≤ 150cc, D5cc ≤ 28-30 Gy
- Longitudinal strip of skin/subcutaneous tissue, defined for extremity tumors only as a 2cm thickness strip on the contralateral aspect of the extremity: V12Gy < 10%, D50% <12 Gy.
- Long bones (femur, humerus): maximum dose 31.5 Gy, D50cc≤28Gy
- Femoral or humeral head: V30Gy < 5cc, maximum <31.5 Gy
- Joints (knee, ankle, hip, shoulder, elbow, wrist): V50% ≤ 32 Gy
- Genitalia (e.g. vulva, perineum): V25Gy ≤ 10%
- Reproductive organs (testes, ovaries): mean (combined right & left) ≤ 2 Gy
- Spinal cord: max 30 Gy
- Chest wall: V30Gy<70cc
- Bowel: max 32 Gy, V30 Gy < 5cc
- Liver: V15Gy < 700cc
- Kidney (bilateral): V10Gy < 10%
- Heart: mean dose <8Gy
- Brachial plexus: max dose <33 Gy, D5cc ≤31.5 Gy

## **5.3 Treatment Verification and Delivery**

Prior to each treatment delivery, daily image guidance will be used to verify the patient's treatment position and appropriate patient alignment. This can include but is not limited to kV imaging, MV imaging, cone beam CT image guidance, or MRI guidance.

Radiation will be delivered daily for 5 consecutive days with the exception of weekends and holidays. In instances where the radiation treatment week contains a holiday or scheduling availability is limited, two fractions of radiation may be given on the same day providing that the fractions are administered  $\geq 6$  hours apart (this is considered standard of care treatment). Treatment will be completed within a maximum of 12 days.

#### **5.4 Patient Follow-up after Treatment**

Patients will be seen in clinic within 3 months after the completion of radiation by either the radiation oncologist or the surgeon. After this, follow-up will be performed every 6 months after the time of surgery for the first 5 years after treatment (+/- 2 months). The patients will be followed both clinically and radiographically after treatment. CT or MRI will be performed of the primary site and CT of the chest every 6 months (+/- 2 months) for the first 2 years and then once at the end of year 3, or at the investigators' discretion. Whenever feasible and in the best interest of subjects, follow-up visits may occur via telemedicine.

